#### Treatment group

In the treatment group, patients receive a bundle of care combining five techniques of cardioprotection (Table 2):
After intravenous induction, anesthesia is maintained during surgery with sevoflurane to induce both preconditioning and postconditioning. During CPB, sevoflurane is administered through the heart–lung machine only in two institutions (Lyon University Hospital and Arnault Tzanck Institute). In the four remaining centers, because the device for administering sevoflurane is not available on the heart–lung machine, propofol is administered during CPB.RIPC is applied using a Riester® pneumatic tourniquet placed on the upper arm (Riester Company, 72,417 Jungingen, Germany). Three cycles of 5-min inflation to 200 mmHg/5 min deflation are performed after anesthesia induction and before skin incision.Intraoperative blood glucose management involves the initiation of insulin infusion when blood glucose, measured every 30 min, is greater than 140 mg/dl.During CPB, 5 min before aortic unclamping, blood gases are adjusted by limiting the flow of air/oxygen mixture in the heart–lung machine, in order to obtain an arterial blood pH lower than or equal to 7.30, and consequently to limit the “pH paradox” phenomenon occurring at the time of reperfusion [11, 12].Just after aortic unclamping, a “gentle reperfusion” protocol is applied, consisting of a gradual recovery of the CPB flow (initial recovery of the flow at 20% of the theoretical flow, with an increase of 20% every 30 s, until a complete restoration of the CPB flow in 2 min) to limit reperfusion injuries.

**Table 2 Tab2:** Perioperative protocol in each of the two treatment arms

	Control group	Treated group
Maintenance of anesthesia	Propofol	Sevoflurane
RIPC	No	Three cycles of: 5 min inflation to 200 mmHg/5 min deflation
Intraoperative blood glucose (BG) management	BG control every 60 min. Intravenous insulin infusion if BG greater than 180 mg/ml	BG control every 30 min. Intravenous insulin infusion if BG greater than 140 mg/ml
pH level at the end of CPB, before aortic unclamping	pH ≥ 7.40	pH ≤ 7.30
Gentle reperfusion	No	Gradual recovery of the CPB flow (initial recovery of the flow at 20% of the theoretical flow, with an increase of 20% every 30 s, until complete restoration in 2 min)

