### Outcomes

The primary outcome is the postoperative 72-h area under the curve (AUC) for high-sensitivity cardiac troponin I (hsTnI) release. Blood samples are collected after induction of anesthesia (baseline) and 4, 8, 12, 24, 48, and 72 h after aortic unclamping (Table 3). All samples are frozen carefully and sent to a centralized laboratory for measurement (see below).

**Table 3 Tab3:** ProCCard trial schedule during the study period

	Preoperative day	Day of surgery				Postoperative day	Hospital discharge	Postoperative day
		Baseline	Before aortic unclamping	ICU arrival	H4-H8-H12	H24-H48-H72		Day 30
Eligibility screen	x							
Informed consent	x							
Randomization		x						
High-sensitivity troponin I		x			x	x		
Blood glucose level		x	x	x				
Arterial lactate		x		x	x (H8)			
Arterial pH			x	x				
Creatininemia	x			x		x		
ECG	x			x		x		
Trans-thoracic echocardiography	x						x	
Quality of life	x							x
Visit before hospital discharge							x	
Phone call								x
Adverse events		x	x	x	x	x	x	x

The secondary outcomes are hsTnI level (peak and 24 h after aortic unclamping), extubation time, length of stay in ICU and hospital, Index Gravity Score (IGS II; the scoring system measuring the severity of disease for patients admitted to ICU), the three-level version of EQ-5D (EQ-5D-3 L) health status score (comparison between preoperative and 30 day postoperative), and the need for catecholaminergic support [13]. Major adverse events occurring during 30 postoperative days are collected and reported as follows: all-cause of death, serious infection requiring antibiotic therapy, major bleeding requiring transfusion of ≥ 5 U packed red blood cells or surgical intervention, respiratory insufficiency, stroke, arrhythmia requiring medical therapy.

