#### Intraoperative data

During surgery, the following data are collected: CPB duration (min), aortic cross-clamping duration (min), type and volume of cardioplegia (ml), surgical procedure performed, baseline hsTnI level, baseline lactate level, total IV sufentanil/remifentanil (μg), total IV propofol (mg), total IV insulin (IU), catecholaminergic treatment, blood glucose concentrations during the operative period, arterial blood gas harvested 5 min before aortic unclamping.

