All secondary outcomes will be summarized, per arm, according to their nature (qualitative or quantitative). The peak of serum level of hsTnI and the level of hsTnI at 24 h after aortic unclamping will be analyzed in the same way as the main outcome. The duration of mechanical ventilation and the duration of stay in the ICU will be similarly analyzed either after log-transformation of the values or using a survival analysis technique (time-to-event analysis of the time to mechanical ventilation discontinuation or the time to discharge from hospital, respectively). A frailty Cox model may be used to allow for the variables used for stratification. The length of hospital stay will be analyzed with a Cox frailty model adjusted for the variables used for stratification. The IGS II will be analyzed in the same way as the main outcome after checking the score distribution. If necessary, an adequate score transformation may be applied.

The need for catecholaminergic support will be analyzed with a logistic model adjusted for the variables used for stratification.

The occurrence of at least one postoperative complication will be analyzed with a logistic model adjusted for the variables used for stratification. The complications considered are: post-operative hemorrhage, need for postoperative blood transfusion, the need for revision surgery for bleeding, the occurrence of respiratory insufficiency requiring intubation or not, postoperative infection, neurological disorder, and complete arrhythmia by atrial fibrillation. The postoperative adverse events will be analyzed in the safety population. The safety population is defined as all patients of the ITT population who received any treatment of the actually applied strategy. The proportions of patients concerned by the secondary outcomes will be calculated by arm and type of complication.

The EQ-5D-3 L score will be analyzed using a mixed linear regression model that will include a variable for “time” (at 30 days after surgery vs before surgery), a variable for “group”, and an interaction between these two variables. This model will also be adjusted for the variables used for stratification. The coefficient of interaction will be tested to compare the arms. The score distribution will be examined for floor and/or ceiling effects. If necessary, a Tobit model will be used. Survival will be analyzed with a Cox model adjusted for the variables used for stratification.

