All the cardioprotective procedures we are combining in this protocol were chosen carefully. The purpose was to combine easily applicable procedures with potential synergistic effects. As mentioned by previous studies, the beneficial effect of RIPC is potentially amplified during halogenated anesthesia. Kottenberg et al. [26] conducted a study during coronary artery bypass graft surgery. Three cycles of 5 min upper arm ischemia/5 min reperfusion decreased the troponin AUC by 50% during isoflurane anesthesia but had no effect under propofol anesthesia. The same results were confirmed later in a larger study [27]. We therefore decided that patients in the “treated group” would be anesthetized with sevoflurane and would also benefit from a RIPC protocol. In parallel, the frequency of perioperative dysglycemia is underestimated in cardiac surgery and its impact on postoperative morbidity and mortality is unquestionable [24]. Because hyperglycemia can impair the myocardial tolerance to ischemia-reperfusion and knowing that insulin is cardioprotective, we included these parameters in the bundle of care of the ProCCard study, in conjunction with RIPC and sevoflurane [28]. Based on the study of Duncan et al. [29], we chose to keep the intraoperative blood glucose threshold at 8 mmol/l in order to avoid any hypoglycemia. Our objective was to control the patient’s glycemia, rather than to conduct a hyperinsulinemic management protocol, as recently proposed [30]. The moment of reperfusion, which corresponds to the aortic unclamping, is also a double-edged sword. Temporary acidosis at the time of reperfusion can limit infarct size by delaying the opening of the mitochondrial permeability transition pore [11]. We have therefore ensured that the pH level is in the low range of clinically acceptable values to limit the “pH paradox” phenomenon [12, 31]. The final procedure in this bundle of care is a gentle reperfusion protocol. Controlled reperfusion after an ischemic period protects the myocardium, probably by the activation of the phosphatidylinositol 3-kinase–Akt pathway [32]. We therefore decided to limit reperfusion injuries by a gradual restoration of the theoretical CPB flow over 2 min.

In conclusion, the ProCCard study will be the first multicenter randomized controlled trial aiming to assess the role of a bundle of care combining several cardioprotective procedures to reduce myocardial damage in patients undergoing CPB.

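### Adverse events are collected from baseline, but the stated safety analysis covers only postoperative ones, so intraoperative events, including hypoglycemia, have no stated between-arm analysis

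*Protocol article*

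**What the plan says.** The protocol article sets a collection window in one place and an analysis window in another.

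- **Collection.** Table 3 (Outcomes) marks adverse events in every column from baseline and before aortic unclamping through to day 30. It schedules blood glucose at baseline, before unclamping and at ICU arrival. The Intraoperative data section adds "blood glucose concentrations during the operative period" to what is recorded.
- **Analysis.** Under Statistical analyses: "The postoperative adverse events will be analyzed in the safety population". That population is then defined: "The safety population is defined as all patients of the ITT population who received any treatment of the actually applied strategy". The logistic model is for at least one postoperative complication, and its list begins: "The complications considered are: post-operative hemorrhage, need for postoperative blood transfusion, the need for revision surgery for bleeding". It continues with respiratory insufficiency, infection, neurological disorder and atrial fibrillation.
- **Reporting.** Under Outcomes: "Major adverse events occurring during 30 postoperative days are collected and reported as follows", followed by death, serious infection, major bleeding, respiratory insufficiency, stroke and arrhythmia.
- **Glucose strategy.** For the treatment group: "Intraoperative blood glucose management involves the initiation of insulin infusion when blood glucose, measured every 30 min, is greater than 140 mg/dl". The control group is measured every 60 min with a trigger of 180 mg/dl. The Discussion explains the choice: "we chose to keep the intraoperative blood glucose threshold at 8 mmol/l in order to avoid any hypoglycemia".

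Hypoglycemia is in neither event list.

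**The concern.** The bundle is delivered entirely in the operating room. A safety analysis that starts after surgery starts once the exposure is over, although the safety population is itself defined by having received that exposure. Events in the first two adverse event columns of Table 3 are collected and then have no stated use in a comparison.

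Hypoglycemia is the clearest case. The arms differ by design in insulin trigger, the article itself names this harm, and the glucose values are recorded. If no comparison is fixed beforehand, any later one will be chosen with the data in view. A simple count of low readings would then be tilted by the different sampling intervals.

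What is at stake is the safety conclusion about the bundle. The troponin result is not affected.

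**Working it through.** **1. Windows side by side**

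| Item | Period | Place in the article |
|---|---|---|
| Preconditioning cycles | after induction, before incision | Treatment group |
| Sevoflurane maintenance | during surgery | Treatment group |
| Glucose strategy | intraoperative | Treatment group, Control group |
| pH adjustment | 5 min before unclamping | Treatment group |
| Gentle reperfusion | the 2 min after unclamping | Treatment group |
| Adverse events collected | baseline to day 30 | Table 3 |
| Major events reported | 30 postoperative days | Outcomes |
| Adverse events analyzed | postoperative | Statistical analyses |

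The whole exposure lies inside the collection window and before the stated analysis window.

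**2. Where glycemia appears in the analysis.** Glycemic monitoring enters one model, as a practice that may influence troponin kinetics. It is not a safety outcome there. No other analysis names it.

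**3. Effect of unequal sampling on a crude count.** Inputs from the article: sampling interval S = 30 min (treatment) and S = 60 min (control). Assumptions: episodes start at random relative to the sampling times, only scheduled readings are taken, and the true rates are equal. The article gives no episode length L, so a range is shown.

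Probability that an episode of length L is detected = min(1, L/S).

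- L = 30 min: 30/30 = 1.0 against 30/60 = 0.5, ratio 2. For shorter episodes the ratio stays (L/30)/(L/60) = 2.
- L = 45 min: 1.0 against 45/60 = 0.75, ratio 1.33. Between 30 and 60 min the ratio is 60/L.
- L = 60 min or more: 1.0 against 1.0, ratio 1.

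The apparent ratio therefore lies between 1 and 2 when the true ratio is 1.

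**4. What a comparison could show with 105 per arm.** The article gives no hypoglycemia rates, so these are assumed. For a two-sided 0.05 test of two proportions by the normal approximation:

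power = Φ((|p2 − p1| − 1.96·SE0)/SE1), with SE0 = √(2·p̄(1 − p̄)/105) and SE1 = √((p1(1 − p1) + p2(1 − p2))/105).

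- 1% against 3%: power about 18%.
- 1% against 5%: p̄ = 0.03, SE0 = 0.02354, SE1 = 0.02338; (0.04 − 0.04614)/0.02338 = −0.263; power about 40%.
- 1% against 10%: p̄ = 0.055, SE0 = 0.03146, SE1 = 0.03085; (0.09 − 0.06167)/0.03085 = 0.918; power about 82%.

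Only a large excess would be detected reliably, so the summary should be presented as descriptive.

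**The case against.** The strongest reply is that this is a condensed article. Full adverse event tables and laboratory summaries usually sit in the full protocol or analysis plan, which are not shown. On this view the sentence about postoperative events only assigns them a population, and does not say that intraoperative events will be dropped. Part of this stands: the silence on hypoglycemia cannot be read as a decision to exclude it. But the word postoperative is a stated scope, narrower than the collection window in the same article, and that mismatch does not depend on what another document adds.

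A reader might infer that hypoglycemia can never enter a comparison, or that the trial cannot speak to safety at all. The article does not support that. A low value at ICU arrival could count as postoperative. Neurological disorder is in the complication list and survival is analyzed, so serious consequences of an intraoperative event can appear in a comparison. Under Regulatory issues, all severe adverse events are documented and declared, and an independent board monitors safety. That oversight is not a stated between-arm analysis, but it is real protection.

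It is also fair to say that the article states no safety hypothesis, that it mentions hypoglycemia as a reason for the threshold and not as an endpoint, and that the sampling bias concerns a count nobody has planned. The bias is therefore a reason to settle the method when the comparison is added. It is not a defect in an existing analysis, and a flat two-fold inflation should not be claimed.

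**Conclusion.** The point holds in limited form. Adverse events are collected from baseline, the stated analysis is confined to postoperative ones, and the gap between the two is the period in which the bundle is applied. No between-arm analysis is stated for intraoperative adverse events in general or for intraoperative hypoglycemia in particular.

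The window mismatch follows from the text and needs no assumption. The factor of 1 to 2 for a crude count rests on an assumed episode length, random timing and scheduled readings only. The power figures rest on assumed rates. The primary and efficacy analyses are untouched. The change is worth making because the safety conclusion would otherwise leave out the exposure period.

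**What to change.** 1. In Statistical analyses, replace the reference to postoperative adverse events with all adverse events from induction to day 30, analyzed in the safety population.
2. Add a descriptive per-arm summary of hypoglycemia from the glucose values already recorded, using a definition set by the sponsor's clinicians.
3. Compare the arms at the scheduled time points common to both once the glucose strategies are running: before aortic unclamping and at ICU arrival. Baseline is also common, but it is sampled after induction, before the strategies can have had much effect, and carries little information.
4. Describe all other readings by arm, for example "BG control every 30 min" in the treatment group against every 60 min in controls, and state this sampling difference beside the table.

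**Cost.** One amended sentence and one table from existing data, with no new measurement and no change in sample size. The common time points will catch fewer episodes than the full set of readings, and with 105 per arm the summary is descriptive and not a powered test. No insulin threshold or other clinical rule is altered.

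### EQ-5D-3L arms are compared by a time-by-group interaction with a free baseline group effect: a valid change-score test that uses the preoperative score inefficiently

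*Protocol article*

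**What the plan says.** The Outcomes section of the protocol article lists the EQ-5D-3L score as a secondary outcome, described as a "comparison between preoperative and 30 day postoperative". Table 3 in the same section puts quality of life on the preoperative day and at day 30, and randomization at the baseline point on the day of surgery. There is thus one score before randomization and one after treatment.

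Statistical analyses specifies a mixed linear model that contains "a variable for “time” (at 30 days after surgery vs before surgery"), then "a variable for “group”, and an interaction between these two variables". It continues: "This model will also be adjusted for the variables used for stratification". The arms are compared as follows: "The coefficient of interaction will be tested to compare the arms". For floor or ceiling effects there is a fallback: "If necessary, a Tobit model will be used".

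Nowhere does the article enter the preoperative EQ-5D score as a covariate or constrain the arms to a common preoperative mean. The terms and the tested coefficient are stated outright, so this is a choice the article makes and not a detail left to a document that is not shown.

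**The concern.** With two time points, the group main effect is the arm difference before surgery and the interaction is the arm difference in change from before surgery to day 30. Because the preoperative score is taken before randomization, any arm difference in it is chance. Estimating that difference freely subtracts each arm's baseline mean in full, which amounts to fixing the slope of the day-30 score on the preoperative score at 1 instead of letting the data set it.

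Two things follow. The confidence interval is wider than the same data allow. And when the arms differ by chance before surgery, the estimated effect is pushed away from the arm that happened to start higher. EQ-5D-3L is the only patient-reported outcome listed, and the sample size was set for the troponin AUC alone, so this comparison has no stated power to spare.

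**Working it through.** **Inputs.** From the documents: two time points, the model terms and the tested coefficient (Statistical analyses); the timing of the score and of randomization (Table 3); 100 evaluable and 105 randomized patients per arm (Sample size). Not in the documents: the standard deviations of EQ-5D-3L before surgery (s0) and at day 30 (s1), and the correlation rho between the two scores. These are assumed over a range.

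**The plan's own figure.** There is none for EQ-5D. The only sample size is for troponin AUC (242 against 169, standard deviation 183). A two-sided t-test with 100 per arm has power 0.802, so that figure reproduces. It does not bear on this point, and 100 per arm serves below only as a yardstick.

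**Step 1: the interaction is the change score.** In simulated complete data, the mixed-model interaction and the simple comparison of mean change gave the same result (for example estimate 0.1063, SE 0.1269 from both). Stratification terms that do not vary over time left it unchanged.

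**Step 2: variances.** Per patient, in large samples:

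- interaction (change): s0² + s1² − 2·rho·s0·s1
- baseline-adjusted day-30 score: s1²·(1 − rho²)
- difference: (s0 − rho·s1)², which is never negative

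**Step 3: equal standard deviations (s0 = s1).** The variances become proportional to 2(1 − rho) and 1 − rho², and adjusted/interaction = (1 + rho)/2.

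| rho | interaction | adjusted | ratio | CI of planned test wider by | 100 per arm is worth | power when adjusted analysis has 80% |
|---|---|---|---|---|---|---|
| 0.3 | 1.40 | 0.91 | 0.65 | 24% | 65 | 62% |
| 0.5 | 1.00 | 0.75 | 0.75 | 15% | 75 | 68% |
| 0.7 | 0.60 | 0.51 | 0.85 | 8% | 85 | 73% |
| 0.9 | 0.20 | 0.19 | 0.95 | 3% | 95 | 78% |

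On this scale the day-30 score with no use of baseline has variance 1. For rho below 0.5 the interaction variance exceeds 1, so the planned test is then less precise than ignoring the preoperative score.

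Simulation at rho = 0.5 with 105 per arm (1,000 data sets) gave an interaction/adjusted variance ratio of 1.35 against 1/0.75 = 1.33 in theory, with mean SEs of 0.138 and 0.120.

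**Step 4: unequal standard deviations.** With s1 = 1.5·s0 (assumed), adjusted/interaction is:

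- rho 0.3: 2.0475/2.35 = 0.87
- rho 0.5: 1.6875/1.75 = 0.96
- rho 0.7: 1.1475/1.15 = 1.00

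With s1 = (2/3)·s0 and rho 0.5 it is 0.3333/0.7778 = 0.43.

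**Step 5: validity and conditional shift.** At rho = 0.5 and 105 per arm, 40,000 simulated data sets with no treatment effect gave a rejection rate of 0.050 for the change-score test. (The 1,000-set run gave 0.069, with a Monte Carlo SE of 0.007; the larger run shows that this was chance.) Given a baseline difference d between arms and equal standard deviations, the interaction estimate shifts by −(1 − rho)·d. The simulated slope was −0.50, and about 0 for the adjusted estimate. At rho = 0.5 the SE of the baseline difference equals the SE of the interaction, so an imbalance of one SE moves the interaction estimate by half of its own SE.

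**The case against.** The strongest reply is that nothing here is an error. The model is prespecified, it matches the outcome as described ("health status score (comparison between preoperative and 30 day postoperative"), and under randomization it is unbiased with the right type I error. That stands. A reader might infer from the regression-to-the-mean argument that the planned test is biased or invalid. The documents do not support this: the shift is conditional on the observed imbalance and averages to zero over randomizations.

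A second reply is that the size is unknown. This also stands. A saving of 15% to 35% holds only for equal standard deviations and correlations between 0.3 and 0.7, and the documents give neither quantity. Step 4 shows that the saving can nearly vanish or be much larger. What survives is the direction: the difference in variance is a square, so in large samples adjustment does not lose. Equality with the change score is exact for complete pairs only; it is approximate when some patients have one score, and under the Tobit fallback.

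A reader might also infer that the model treats patients who died before day 30 as ordinary missing scores, and ask for deaths to be scored as 0. The article does not say how deaths enter this analysis, and a journal article may leave that to the full protocol or analysis plan, so silence is no finding. Scoring deaths as 0 would also change the quantity being estimated.

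**Conclusion.** The point holds as a matter of efficiency. The stated EQ-5D-3L comparison is a change-score test for complete pairs. It is valid, but it makes poor use of a score measured before randomization and moves with chance imbalance in that score. Under the assumption of equal standard deviations, 5% to 35% of the variance could be saved for correlations from 0.9 down to 0.3. Without that assumption the saving ranges from about nothing to more than half in the cases worked above. The consequence is confined to the interval and power for one secondary outcome with no stated power. The troponin analysis and the sample size are untouched.

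**What to change.** Replace the tested contrast by one of two equivalent choices, fixed before the data are compared by arm:

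- Keep the longitudinal model but drop the group main effect, so that both arms share one preoperative mean. Use an unstructured covariance for the two time points and test the day-30 arm effect.
- Regress the day-30 score on arm, preoperative score, center and need for coronary bypass, and test the arm coefficient.

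If the Tobit fallback is used, enter the preoperative score as a covariate there too.

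The cost is a change in one model term; no new data, visits or patients are needed. The regression form spends one degree of freedom on the slope and leaves out patients without a preoperative score unless it is imputed. The longitudinal form keeps patients who have only one of the two scores.
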